## Methods/design

This trial protocol has been approved by the University of Calgary’s Conjoint Health Research Ethics Board (Ethics ID: REB13-1211-Mod3), the University of Saskatchewan’s Biomedical Research Ethics Board (Bio-No. 14-212), plus the Research Review Committee, the Ethics Review Committee, and the Data and Safety Monitoring Board (DSMB) of the International Centre for Diarrhoeal Disease Research, Bangladesh (Icddr,b) (Protocol No. PR-14013). Any changes to the trial protocol are communicated to the relevant parties and ethics boards. The trial will be reported according to SPIRIT (Standard Protocol Items: Recommendations for Intervention Trials) 2013 [21] (see Additional file 1). A summary of the trial according to the WHO Trial Registration Minimal Data Set is provided in Table 1 [22].

**Table 1 Tab1:** WHO Trial Registration Minimal Data Set according to Moja et al*.* [22]

Data	Information
Trial identification number	ClinicalTrials.gov NCT02429921
Trial registration date	April 21, 2015
Secondary IDs	REB13-1211 (CHREB, University of Calgary), PR-14013 (ERC, icddr,b)
Funding sources	Global Institute for Food Security (GIFS); Grand Challenges Canada - Stars in Global Health Round 5
Primary sponsor	[name], Faculty of Vet. Med, University of Calgary, Canada
Secondary sponsor	RR, icddr,b, Dhaka, Bangladesh
Responsible contact person	RR, icddr,b; [contact]
Research contact person	[name], Faculty of Vet. Med., University of Calgary; [contact]
Brief title of the study	High-selenium Lentils Versus Arsenic Toxicity
Official title of the study	Mitigating arsenic toxicity in Bangladeshi people by supplementing their diets with high selenium lentils
Country of recruitment	Bangladesh
Health problem studied	Chronic arsenic poisoning
Intervention	High-selenium lentils, control: low-selenium lentils
Key inclusion and exclusion criteria	Inclusion criteria: families with >100 ppb As in their well water; ages eligible for study: 14–75
	Exclusion criteria: As content of well water ≤100 ppb; ill health detected during initial recruitment health check
Study type	Double blind, parallel, block-randomized, controlled intervention trial
Trial start date	September 28, 2015
Target sample size	200 per treatment group (400 in total)
Recruitment status	Active
Primary outcome	Arsenic body burden: We will determine if high-Se lentil consumption will decrease the body burden of As by measurement of As excretion in urine and feces and deposition in hair

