### Data analysis

Data are stored in a password-protected database at icddr,b, through a platform that allows sharing of data between project investigators (PIs) at icddr,b and the University of Calgary. Statistical analyses will be done using the statistical software SPSS for Windows PASW version 20. Normality and homogeneity of variances will be determined. Data not normally distributed will be transformed as necessary. Initially Spearman’s correlation analyses will evaluate univariate association between arsenic exposure (urinary and hair arsenic) and outcome variables (oxidative stress, antioxidant status, lung inflammatory status, and genetic variables). Covariates (e.g., demographic and socioeconomic variables, morbidity, daily diet, and BMI of participants) will be evaluated for significant association with exposure and outcomes. Missing data are excluded from that specific analysis. Significantly correlated variables will be further analyzed in multiple linear regression models controlling for potential confounding variables stratified by sex. Potential confounders will be identified based on correlations (*p* < 0.15) with the exposure (toxic metal) and outcomes and will be included in the final models when they change the effect estimate for metal exposure on the outcome by 5 % or more.

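### An arsenic-outcome pair reaches the adjusted regression only if an unadjusted correlation in the same data is significant

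*Protocol article*

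**What the plan says.** The Data analysis section of the protocol article sets out two steps. The first is a screen: "Initially Spearman’s correlation analyses will evaluate univariate association between arsenic exposure (urinary and hair arsenic) and outcome variables". The outcomes it lists are "oxidative stress, antioxidant status, lung inflammatory status, and genetic variables". The second is the gate: "Significantly correlated variables will be further analyzed in multiple linear regression models controlling for potential confounding variables stratified by sex".

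Covariates have a rule of their own in the next sentence: "Potential confounders will be identified based on correlations (*p* < 0.15) with the exposure (toxic metal) and outcomes", followed by a criterion of at least a 5% change in the estimate. Two further statements bear on the check: "Data not normally distributed will be transformed as necessary" and "Missing data are excluded from that specific analysis".

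The section gives no significance level for the screen. It mentions no hold-out sample and no allowance for the selection, and it does not call these analyses exploratory.

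**The concern.** The regression is there to remove confounding, and the section itself names demographic and socioeconomic variables, morbidity, diet and BMI as candidates. The test that opens the way to the regression removes none of it. If confounding pulls the unadjusted correlation towards zero, the pair is stopped before the one analysis that could show the association.

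The pairs that do go forward were chosen because they were significant in the same participants. Their regression p-values and slopes then no longer mean what they would in a model fitted regardless of the data.

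Oxidative stress, antioxidant status and lung inflammation are named among the trial's secondary objectives, and the Discussion intends the results to inform policy. Which of these markers gets an adjusted analysis should not depend on an unadjusted p-value.

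**Working it through.** **Inputs.** From the protocol: 400 participants (Table 1), a Spearman screen, then adjusted linear regression stratified by sex, with transformation of non-normal data. Assumed, because the article does not give them: a two-sided 0.05 screen, normal data after transformation, two equal sex strata of 200, independent observations (household clustering not modelled), and all confounding strengths.

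The article states no figure for this screen. Its only recomputable figure, 26 per group for hair arsenic, reproduces: (1.4² + 0.73²)(1.645 + 0.842)²/0.78² = 25.3, rounded up to 26. It plays no part below.

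**Step 1: associations lost to masking.** Take standardised arsenic, a true adjusted slope b = 0.20, residual SD 1, and three independent covariates. Each has correlation a with arsenic and coefficient −g on the outcome. The unadjusted covariance is b − 3ag.

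For a = g = 0.2:
- Direct regression: SE = 1/(√400 × √(1 − 3 × 0.2²)) = 1/(20 × √0.88) = 0.0533. Then 0.20/0.0533 = 3.75, and power ≈ Φ(3.75 − 1.96) = 0.96. Simulation gave 0.960.
- Screen: covariance = 0.20 − 0.12 = 0.08. Outcome variance = 1 + 0.04 + 0.12 − 0.048 = 1.112, so r = 0.08/√1.112 = 0.076. The Spearman value is (6/π) arcsin(r/2) = 0.0725. Pass rate ≈ Φ(20 × 0.0725 − 1.96) = Φ(−0.51) = 0.305. Simulation gave 0.305.

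| Assumed masking (b = 0.20, n = 400) | Unadjusted covariance | Pass the screen |
|---|---|---|
| a = 0.2, g = 0.2 | 0.08 | about 30% |
| a = 0.2, g = 0.1 | 0.14 | about 75% |
| a = 0.1, g = 0.1 | 0.17 | about 88% |

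Direct pooled power is about 96–97% in these cases. Within one sex of 200 it is about 74%.

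The extreme is full suppression: one covariate with correlation 0.5 with arsenic and coefficient −2b on the outcome, so the covariance is b − 0.5 × 2b = 0.

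| Adjusted slope | Significant if modelled directly | Pass the screen | Significant if modelled, but stopped by the screen |
|---|---|---|---|
| 0.10 | 42% | 5.8% | 39% |
| 0.15 | 73% | 4.9% | 70% |
| 0.20 | 94% | 5.0% | 90% |

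**Step 2: null pairs that pass.** With no covariates and no stratification, the Spearman and regression statistics have null correlation 3/π = 0.955. The probability that both are significant is 0.0362, so the rate among pairs that pass is 0.0362/0.05 = 72%. Simulation with n = 400 and 20,000 replicates gave:

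| Model after the screen | Significant among passers, pooled | One sex | At least one sex | Null pair clears both steps (pooled) |
|---|---|---|---|---|
| No covariates | 72% | 30% | 58% | 3.5% |
| 5 irrelevant covariates | 70% | 27% | 56% | 3.5% |
| Covariates explain 20% of outcome variance | 53% | 28% | 51% | 2.6% |
| Covariates explain 40% | 35% | 18% | 34% | 1.8% |

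Without a gate the benchmarks are 5% for a single model and 1 − 0.95² = 9.75% for at least one sex. A separate run with three covariates gave 0.051 × 0.716 = 3.7% for both steps. If screen and model are both run within one sex (n = 200), the rate among passers is 68% with irrelevant covariates and 53% when they explain 20% of the variance.

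**Step 3: exaggeration.** With a true slope of 0.10 and n = 400, 47.6% of pairs pass. Their mean estimate is 0.140, and 0.140/0.100 = 1.40, an overstatement of 40%.

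**The case against.** **The wording could mean something else.** The gating sentence follows closely on one about testing covariates, so the variables it refers to might include covariates. It also does not say outright that other pairs will not be modelled. But covariates have their own selection rule in the very next sentence, and no model is planned for pairs that fail. The plain reading is that pairs are gated. If that was not meant, the sentence still needs correcting.

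**The 72% is an upper end.** This stands. It belongs to a pooled model with no useful covariates, whereas the plan adjusts and stratifies by sex, which brings the figure down to about 18–30% in one sex. It also rests on an assumed screening level.

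**The masking figures come from chosen scenarios.** This stands too. No confounding strength is given in the article, and under mild masking most real associations still pass. The mechanism is certain, but its size in this trial is unknown.

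**The family-wise error rate.** A reader might blame the gate for the chance of some false finding across four outcome groups and two exposures. For eight null tests that chance is 34%, 25% or 16% at correlations of 0, 0.5 or 0.8. Eight ungated regressions have the same rate, and at correlation 0.5 the two steps together lower it from 25% to 19%. It is not a harm of the gate.

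**The article condenses a fuller plan.** An exploratory label may exist elsewhere. The gate itself, however, is a rule that this text states, not a detail it leaves out.

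**Conclusion.** The point holds for the secondary analyses that relate arsenic markers to the four listed groups of variables. The more serious consequence is loss: under the assumptions above, the screen passes between about 5% (full suppression) and 88% (mild masking) of pairs with a true adjusted slope of 0.20, which direct pooled regression would detect 94–97% of the time. The lesser one is that the fitted models are read as if unselected, when some 18–72% of null passers would be significant and modest slopes would be overstated.

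Three stronger readings are not supported:
- A reader might infer that false positives per test are inflated. They are not: a null pair clears both steps in about 2–4% of cases. The high percentages apply only to the roughly 5% of null pairs that pass.
- A reader might infer that the trial's main result is at risk. The section describes exposure-outcome associations, not the randomised comparison of lentil groups, and the primary outcome of arsenic in urine, faeces and hair is not itself gated. Lipids, blood pressure, acute phase proteins and BMI are not in the screened list either.
- A reader might infer that non-significant outcomes go unreported. The text does not say so; Spearman analyses are planned for all the listed variables.

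The sentence should be changed, but the flaw does not undermine the primary analysis.

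**What to change.** Replace the gating sentence with one stating that the confounder-adjusted, sex-stratified model will be fitted for every listed outcome with urinary and with hair arsenic, whatever the Spearman p-value. Report all estimates with confidence intervals. Keep the Spearman correlations as description only, and label these association analyses exploratory.

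This needs no new data. The cost is one reworded sentence, a few more regressions and a longer results table that includes null results. The article describes recruitment as still under way, so the change can be made before the final data are in.

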## Discussion

This trial is the first to use a high-selenium food source, i.e., lentils, in an attempt to combat the adverse health effects of chronic arsenic poisoning. Since lentils are an excellent source of non-animal protein and micronutrients such as Zn and Fe [35], we expect to see an improved BMI after 6 months of supplementation and possibly improved overall health status in all participants of the trial, regardless of the selenium content of the lentils. As a result, some of the proposed biomarkers may not be significantly different between the control and the high-selenium groups. However, since selenium can form a complex with arsenic, selenium supplementation, in principle, can reduce arsenic toxicity. We expect to see a significant decrease in the body burden of arsenic, the primary outcome of this study, in the high-selenium group. Mild beneficial effects of selenium have been indicated in a number of supplementation trials with selenium alone or in combination with other micronutrients [36–38]; more trials are needed for conclusive evidence.

If we can prove that health benefits occur due to consumption of high-selenium lentils in arsenic-exposed communities, the first step will be to inform the Bangladeshi public — through a follow-up meeting with the participants and local media — and to promote consumption of higher-selenium food sources. Here again, the female family head will be the one responsible for purchasing and preparing nutritious food for the family.

Furthermore, we will disseminate the study results to the Food Planning and Monitoring Unit (FPMU) of the Ministry of Food, the Government of Bangladesh, and provide evidence-based advice for policy formulation on lentil import and agricultural aspects. The results may guide Bangladeshi importers to specifically target importation of high-selenium lentils.

The long-term goal toward food security will entail working on agronomic techniques to increase the production of high-selenium lentils in Bangladesh.

## Trial status

Participants are currently being recruited.

## Abbreviations

8-OHdG: 8-hydroxy-2'-deoxyguanosine
BMI: body mass index
BP: blood pressure
CRP: C-reactive protein
GFAAS: graphite furnace atomic absorption spectrometry
GSH: reduced glutathione
GSSG: oxidized glutathione
HDL: high-density lipoprotein
HGAAS: hydride generation atomic absorption spectrometry
HH: household
LDL: low-density lipoprotein
ppb: parts per billion
RDA: recommended daily allowance
ROS: reactive oxygen species
